### Sample size

#### Proposed sample size

The study will recruit up to 840 patient–participants: about 280 per season for three consecutive influenza seasons. With 1:1 allocation to groups, there will be 420 patients per group. On the conservative assumption of a 25% positivity rate for influenza during influenza season (ie, ~100 influenza-positive patients in each group), the group sizes would give a 90% power at a 0.05 significance level to detect a difference of 20% in appropriate NAI use (from 65% to 85%) and an 80% power to detect a difference of 17%. In our previous work, 91% of influenza-positive patients randomised to POCT were appropriately treated with NAI versus 65% with routine clinical care, a difference of 26% (95%CI 10 to 43). We suspect that the difference may be larger in this study as there will likely be a number of undiagnosed (and therefore untreated) cases in the control group revealed by testing them with the FilmArray at a later date. In the event of higher numbers of influenza-positive patients being recruited in the first two seasons, the study may be stopped prematurely (once ~100 influenza-positive patients have been recruited to the intervention group).

### Recruitment and screening

#### Screening

Eligible patients in the AMU and the ED will be identified by research staff via regular review of the comprehensive admissions information technology (IT) systems daily. Recruitment will run for up to 3 years to include three seasonal influenza seasons between December 2017 and May 2020.

#### Consent

The study team (research nurse, research fellow or the principal investigator) will obtain informed consent for those fulfilling eligibility criteria and willing to be recruited for those with capacity, or assent via consultee for those without capacity, as per the dedicated study forms. In view of the acute nature of patients’ illnesses, the potential benefits of rapid identification of viruses including prompt NAI use for influenza, the usual 24 hours consideration period for a participant or consultee, will not apply.

Discussion of the study will be provided to patients, or their consultee for those lacking capacity, by study staff. This includes supply of a participant information sheet for the participant or witness to read and retain. Consent is also acquired to obtain and store specimens (nose/throat swab, sputum sample, blood tests) for future research studies.

Each patient will be assumed to have capacity unless it is established that they lack capacity. For patients unable to consent for themselves, this study complies with the Mental Capacity Act 2005 and in such cases, the patient’s family member, carer or friend may be asked to act as the personal consultee and provide assent. In the event of a personal consultee not being available, a nominated consultee (usually the consultant caring for the patient and independent from the study) will be asked if they would provide assent. Both the person taking assent and the consultee must personally sign and date the relevant form.

### Assignment of interventions

#### Sequence generation, allocation concealment and implementation

Following screening and obtaining informed written consent from an eligible patient, a unique identification number will be assigned consecutively. A research team member will then use this identification number to randomise the participant to either the intervention or control group, via an internet-based randomisation service (sealedenvelope.com). This service uses permuted blocks of varying sizes and generates a randomisation code which corresponds to one of the study arms. Research staff will use the allocation code generated from sealedenvelope.com to assign the patients to the intervention or control group.

#### Blinding

As this is a pragmatic trial of a diagnostic strategy where the results of the test must be communicated to clinical and infection control teams, no attempt at blinding trial participants, research staff or care providers will be made. Data analysts will be blinded to group allocation.

#### Data collection, management and analysis

##### Data collection methods

Demographic and clinical data will be collected for all patients at enrolment from paper and electronic medical records including: age, sex, ethnicity, smoking status, vaccination status, comorbidities, medication use, symptoms, duration of illness prior to hospitalisation, observations (pulse rate, respiratory rate, blood pressure, oxygenation status), laboratory results, radiology results, antimicrobial and antiviral use prior to hospitalisation and provisional diagnosis. Data will be recorded on a standardised case report form (CRF) and transferred to a secure electronic database. Once patients have been discharged or after 30 days (whichever is soonest), outcome data will be collected retrospectively from electronic and physical case notes, electronic prescribing systems and laboratory and radiological results systems including: use of antivirals, duration of antivirals, time from assessment to antiviral use, use of antibiotics, duration of antibiotic use, use of side room facilities, time from assessment to isolation facility use, time to clinical stability, duration of supplementary oxygen use, duration of hospitalisation, complications including ICU and HDU admission, representation and readmission to hospital within 30 days, final diagnosis and mortality. The number of diagnostic tests and procedures performed will also be recorded and data will also be collected on the turnaround time of respiratory virus test results in each group. Patients withdrawn from the study will have no further data collected.

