#### Interventions

##### For both control and intervention groups

A respiratory sample will be collected by a member of research staff. A combined nose and throat swab will be taken and placed into viral transport medium. If feasible, a lower respiratory tract sample (sputum) will also be obtained.

Clinical and demographic data will be collected at the time of enrolment. Outcome data will be collected from case notes and electric health records retrospectively.

A blood sample (maximum of 21 mL) will be obtained from all willing participants, processed in the National Institute for Health Research (NIHR) Wellcome Trust Clinical Research Facility lab and stored at −80°C pending further analysis. All respiratory samples leftover from FilmArray testing may be frozen and stored for further study. Participant consent for this is included in the consent form. Patients may be approached for additional samples to be collected and stored for further study (see next for schedule of additional samples).

A letter detailing that the patient has been included in this trial will be sent to the patient’s general practitioner for information only.

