#### Additional procedures

For participants randomised to receive the intervention, who subsequently have a pathogen detected on the FilmArray respiratory panel and for all participants randomised to routine clinical care, additional respiratory samples ±an additional blood test (maximum 10 mL) may be specifically requested from the participants to study temporal changes in viral load, according to the schedule described next.

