### Participant timeline

Participants are identified in the AMU and ED according to eligibility criteria by research staff. Following gaining written consent, participants are immediately randomised to the intervention group or the control group. For those patients randomised to the intervention group, a nose/throat swab is collected by a study doctor or research nurse and this is tested on the FilmArray machine. If the patient is able to produce a sputum sample, this sample will also be tested on the FilmArray machine. Results are generated in approximately 45 min and are immediately communicated to the clinical team. Clinical data are collected prospectively and retrospectively for both groups. Further nose/throat swabs, sputum samples and blood tests may be collected from patients who remain inpatients on serial follow-up visits up to day 14.

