### Statistical methods

Analysis will be by intention to treat (ITT). The framework is superiority. Trial results will be reported in accordance with the Consolidated Standards of Reporting Trials (CONSORT) statement.^39^

Statistical analysis will be performed by a dedicated medical statistician from the University of Southampton, independent from the study team. No interim analysis is currently planned. Patients tested with the rapid molecular diagnostic test will be compared with patients managed according to standard clinical care using standard descriptive and comparative statistical methods using Prism (GraphPad Software, La Jolla, California), and Stata (StataCorp).

Missing data were minimal (<2%) in the CI’s previous POCT study involving 720 patients presenting to secondary care, and is not expected to be significant higher in this trial; however, the use of multiple imputation will be performed should missing data exceed 5% for the primary outcome or key secondary outcome measures.^40^

Summaries of all baseline characteristics will be presented using means and SD, medians and IQRs, or frequencies and percentages, as appropriate. The intervention and control groups will be compared using ORs and differences in proportions for equality of proportions for binary data (eg, proportion of cases of influenza detected) and using independent-sample t-tests or non-parametric equivalent as appropriate for continuous data (eg, duration of antibiotics, test turnaround time, etc).

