### Primary outcome

The primary outcome (proportion of patients infected with influenza treated with NAIs) will be measured only in patients with confirmed influenza, that is, the intention-to-treat-infected (ITTI) population. Difference in proportions and unadjusted ORs will be used to compare the groups. The effect of group on the primary outcome will be further assessed using multiple logistic regression to control for the following covariates: age, sex, influenza vaccine status, receipt of antibiotics prior to admission, duration of illness, comorbidity, temperature, C reactive protein, severity of illness and clinical group.

Certain secondary outcome measures will be measured both in the entire cohort (ITT population) and in the influenza-infected cohort (the ITTI population) while others will only be measured in the ITTI population, as detailed in the outcome section. The intervention and control groups will be compared as per the primary outcome for equality of proportions for binary data and using t-tests and non-parametric equivalent tests for continuous data (eg, turnaround time) as appropriate.

In view of the clinical heterogeneity of patients infected with influenza, heterogeneity of effect among different clinical subgroups is anticipated a priori and therefore a preplanned subgroup analysis for key secondary outcome measures may be undertaken based on clinical group (exacerbation of asthma, exacerbation of COPD, pneumonia, ILI, non-pneumonic LRTI and ‘other’) and also based on receipt or otherwise of antiviral treatment (the receipt of NAIs within 5 days of admission). The interaction between clinical subgroups and allocation group will be assessed in the multiple regression models detailed above.

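### The unqualified rule that withdrawn patients have no further data collected undermines the ITT/ITTI analysis, because most outcomes are read from routine records only after discharge or day 30

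*Protocol article*

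**What the plan says.** Under Data collection methods, the article states without qualification: "Patients withdrawn from the study will have no further data collected". The wording is passive, is not limited to a patient's own refusal, and does not distinguish leaving study procedures from refusing use of records.

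The same section fixes when outcomes are obtained: "Once patients have been discharged or after 30 days (whichever is soonest), outcome data will be collected retrospectively from electronic and physical case notes". The list that follows covers use and timing of antivirals, antibiotics, isolation, clinical stability, length of stay, readmission and mortality. The section on procedures for both groups agrees: "Outcome data will be collected from case notes and electric health records retrospectively". Participant timeline is a little wider: "Clinical data are collected prospectively and retrospectively for both groups".

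Statistical methods commits the trial to intention-to-treat analysis. It reports under 2% missing data in an earlier trial of 720 patients, expects no material increase, and plans multiple imputation if more than 5% is missing for the primary or key secondary outcomes. The primary outcome, NAI treatment within 5 days of admission, "will be measured only in patients with confirmed influenza, that is, the intention-to-treat-infected (ITTI) population".

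Influenza status is established at different times by arm. In the intervention arm the swab is tested promptly. In the control arm the stored swab is tested no earlier than 30 days after collection.

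**The concern.** Intention-to-treat analysis needs an outcome for each randomised patient wherever one can be had. Here the outcomes sit in hospital systems and need no contact with the patient. Because abstraction comes late, someone withdrawn on day 3 has no abstracted primary outcome, even if an NAI had already been given and charted. Such patients can then be analysed as randomised only by imputation, or not at all. A statistical analysis plan cannot repair this, because it cannot recover data that the protocol forbids collecting.

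A second consequence concerns who is in the primary analysis set. If the delayed control swab test counts as further data, a withdrawn control patient with influenza may never be identified by the study and so leaves the ITTI set, unless a routine laboratory result had already been recorded. A withdrawn intervention patient with influenza has a result and stays in the set with a missing outcome. Membership of the primary population could then depend on allocation, and the control losses would not even be visible as missing data.

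**Working it through.** **Inputs from the article (Sample size, Statistical methods).** 420 patients per group; 25% influenza-positive, so 0.25 × 420 = 105, given as about 100 per group; 65% v 85% treated (20 points) at 90% power; a 17-point difference (65% v 82%) at 80% power; significance level 0.05, taken as two-sided; under 2% missing expected; imputation above 5%.

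**Assumption.** The article gives no withdrawal rate. I use w = 2% and w = 5% of influenza-positive patients lost in each arm.

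**1. The plan's own figures.** With pooled variance, power = Φ{[Δ√n − 1.96√(2p̄(1−p̄))] / √(p₁(1−p₁) + p₂(1−p₂))}.

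- n = 100, 65% v 85%: (2.000 − 1.200)/0.596 = 1.342, power 91.0%.
- n = 100, 65% v 82%: (1.700 − 1.223)/0.612 = 0.778, power 78.2%.
- n = 105: 92.3% and 80.1%.

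Both stated powers reproduce to within about 2 points.

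**2. Loss of power, using n(1 − w).**

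| Lost per arm | n per arm | Power, 20 points | Power, 17 points |
|---|---|---|---|
| 0 | 100 | 91.0% | 78.2% |
| 2% | 98 | 90.5% | 77.4% |
| 5% | 95 | 89.6% | 76.1% |

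At 2% the loss is about 0.6 and 0.8 points. Power is not the issue.

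**3. Extreme-case bounds on the treatment difference.** Suppose 85% and 65% are seen among those with data.

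- Lower bound (lost intervention patients all untreated, lost control patients all treated): 0.20(1 − w) − w.
- Upper bound (the reverse): 0.20(1 − w) + w.
- w = 2%: 0.196 − 0.020 = 17.6 points; 0.196 + 0.020 = 21.6 points.
- w = 5%: 0.190 − 0.050 = 14.0 points; 0.190 + 0.050 = 24.0 points.

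**4. Direction when loss is selective in one arm.** Observed rate = (p − wr)/(1 − w), where p is the true rate and r is the treated share among those lost. The values of r are illustrative.

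- Control, w = 5%, r = 30%: (0.65 − 0.015)/0.95 = 66.8%. With r = 0: 0.65/0.95 = 68.4%. The observed difference shrinks by 1.8 to 3.4 points.
- Intervention, w = 5%, r = 0: 0.85/0.95 = 89.5%. The observed difference grows by 4.5 points.

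The sign of any bias therefore cannot be predicted.

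**5. Number of patients affected in the ITTI set.** 0.02 × 105 = 2.1 and 0.05 × 105 = 5.25 per arm. Under the stricter reading of the stored-swab rule, the control patients in this count would leave the denominator, while the intervention patients would remain in it.

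**The case against.** The strongest reply is that stopping collection is the proper response when someone refuses further use of their records. That stands; the defect is that the rule applies equally to everyone else.

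Second, withdrawal creates missing data within an intention-to-treat analysis, and the article anticipates little of it and has an imputation rule. This also stands. A reader might infer that the rule defeats intention-to-treat altogether; at the expected level of missingness it does not. Nor do the documents show that losses at or below 5% would simply be omitted: no method is stated there, and an unseen analysis plan may give one.

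Third, a reader might infer that every outcome is lost. Intervention-arm virology is available soon after enrolment and some clinical data are gathered prospectively. The sentence bars further data and does not say that earlier data are discarded.

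Fourth, a reader might infer that the heavier sampling burden makes control patients withdraw more often, since Additional procedures allows requests "for all participants randomised to routine clinical care, additional respiratory samples" but, in the intervention arm, only where a pathogen is found. The Schedule lets participants decline any of these tests, so tiring of swabs need not mean withdrawal. Sampling burden is not an established cause of differential loss.

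Fifth, an article condenses, and the full protocol or withdrawal form may define types of withdrawal. That is possible, but the article states a definite rule on this point, and the rule as printed is the one criticised.

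Finally, the 4-point gap between 17.6 and 21.6 might be read as the possible shift. It is the width of the interval; the largest shift from 20 is 2.4 points.

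**Conclusion.** The point holds in limited form. As printed, the rule withholds the primary outcome and most secondary outcomes for anyone withdrawn before abstraction, although those outcomes are in routine records, and so undermines the stated ITT/ITTI analysis. The arm asymmetry in influenza status is conditional: it arises only if testing a stored swab after withdrawal counts as further data, which the article does not settle.

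All sizes rest on assumed withdrawal shares and the planning rates of 65% and 85%. At 2% per arm the observed 20-point difference could shift by at most 2.4 points, with under 1 point of power lost. At 5% it could shift by up to 6.0 points. The earlier trial's missing-data figure points to the lower end, and it covers missing data from all causes. This is a cheap improvement that removes avoidable and possibly selective missing data; it does not threaten the trial's validity at the expected rates.

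**What to change.** Replace the sentence with text of this kind: *Unless the patient or consultee specifically refuses further use of routine records or stored samples, outcome data continue to be taken from routine records, the enrolment swab is tested, data collected before withdrawal are kept, and the patient stays in the ITT/ITTI analysis. Withdrawals are reported by arm and type.*

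This respects a genuine refusal and also settles the fate of the control swab. The cost is a minor amendment to the protocol and to the consent or withdrawal forms, plus slightly more note abstraction. It needs no extra patients, procedures or patient contact.

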##### Data management

The study will be conducted in compliance with the approved protocol, relevant International Conference on Harmonisation (ICH) and Good Clinical Practice (GCP) regulations and standard operating procedures. Data will be evaluated for protocol compliance and accuracy in reference to the source documents.

The subjects' anonymity will be maintained. The study team will keep a log of each subject’s name, hospital identification (ID) number, date of birth and unique participant trial number. The participant details will be recorded on the secure NHS Edge system in a similar manner, including NHS number. This participant trial number is used on documents after screening to maintain confidentiality. Documents that are not anonymous (eg, signed informed consent forms) will be maintained separately, in strict confidence and in accordance with the Data Protection Act 1998. A secure database will be used to enter data from the CRFs at the completion of the study, followed by data lock.

The study staff will be responsible for entering study data in the CRF. It is the investigators’ responsibility to ensure the accuracy of the data entered in the CRF.

Only the research study team will know the identity of subjects and have access to the list linking participant details to the participant trial number.

### Statistical methods

Analysis will be by intention to treat (ITT). The framework is superiority. Trial results will be reported in accordance with the Consolidated Standards of Reporting Trials (CONSORT) statement.^39^

Statistical analysis will be performed by a dedicated medical statistician from the University of Southampton, independent from the study team. No interim analysis is currently planned. Patients tested with the rapid molecular diagnostic test will be compared with patients managed according to standard clinical care using standard descriptive and comparative statistical methods using Prism (GraphPad Software, La Jolla, California), and Stata (StataCorp).

Missing data were minimal (<2%) in the CI’s previous POCT study involving 720 patients presenting to secondary care, and is not expected to be significant higher in this trial; however, the use of multiple imputation will be performed should missing data exceed 5% for the primary outcome or key secondary outcome measures.^40^

Summaries of all baseline characteristics will be presented using means and SD, medians and IQRs, or frequencies and percentages, as appropriate. The intervention and control groups will be compared using ORs and differences in proportions for equality of proportions for binary data (eg, proportion of cases of influenza detected) and using independent-sample t-tests or non-parametric equivalent as appropriate for continuous data (eg, duration of antibiotics, test turnaround time, etc).

### Primary outcome

The primary outcome (proportion of patients infected with influenza treated with NAIs) will be measured only in patients with confirmed influenza, that is, the intention-to-treat-infected (ITTI) population. Difference in proportions and unadjusted ORs will be used to compare the groups. The effect of group on the primary outcome will be further assessed using multiple logistic regression to control for the following covariates: age, sex, influenza vaccine status, receipt of antibiotics prior to admission, duration of illness, comorbidity, temperature, C reactive protein, severity of illness and clinical group.

Certain secondary outcome measures will be measured both in the entire cohort (ITT population) and in the influenza-infected cohort (the ITTI population) while others will only be measured in the ITTI population, as detailed in the outcome section. The intervention and control groups will be compared as per the primary outcome for equality of proportions for binary data and using t-tests and non-parametric equivalent tests for continuous data (eg, turnaround time) as appropriate.

In view of the clinical heterogeneity of patients infected with influenza, heterogeneity of effect among different clinical subgroups is anticipated a priori and therefore a preplanned subgroup analysis for key secondary outcome measures may be undertaken based on clinical group (exacerbation of asthma, exacerbation of COPD, pneumonia, ILI, non-pneumonic LRTI and ‘other’) and also based on receipt or otherwise of antiviral treatment (the receipt of NAIs within 5 days of admission). The interaction between clinical subgroups and allocation group will be assessed in the multiple regression models detailed above.

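### The supportive adjusted model for the primary outcome puts at least 15 coefficients on about 50 untreated patients, so ordinary maximum likelihood moderately overstates its odds ratio

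*Protocol article*

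**What the plan says.** All references are to the protocol article.

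- **Statistical methods, Primary outcome.** The arms are compared first by a difference in proportions and an unadjusted odds ratio, in patients with confirmed influenza only. The effect of allocation is then assessed further by multiple logistic regression. The covariates are age, sex, influenza vaccine status, "receipt of antibiotics prior to admission, duration of illness, comorbidity, temperature, C reactive protein, severity of illness and clinical group".
- **Same section, last paragraph.** Clinical group has six levels (asthma exacerbation, COPD exacerbation, pneumonia, influenza-like illness, non-pneumonic lower respiratory tract infection, other). A subgroup analysis by clinical group is optional and is named for key secondary outcomes. The paragraph closes: "The interaction between clinical subgroups and allocation group will be assessed in the multiple regression models detailed above".
- **Proposed sample size.** "With 1:1 allocation to groups, there will be 420 patients per group". The article makes a "conservative assumption of a 25% positivity rate for influenza during influenza season" ("ie, ~100 influenza-positive patients in each group") and plans on 65% v 85% treated. The previous trial saw 65% v 91%.

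The article names no penalised fit and no reduction of the covariate list.

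**The concern.** Precision and bias in logistic regression depend on the size of the rarer outcome class, not on the total sample. Here the rarer class is the untreated patients, and there are few of them for the number of coefficients. Ordinary maximum likelihood then pushes estimates away from zero, and terms in small groups can become infinite.

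The adjusted odds ratio will be reported beside the unadjusted one. If it is larger, readers may take it as confirmation that adjustment strengthens the effect, when part of the gap is small-sample bias. If the subgroup interaction is fitted to the same outcome, it will often give no usable estimate, and a remedy chosen after the model has failed would be data-driven.

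**Working it through.** **1. The plan's own power figure.** Two proportions, pooled variance under the null, two-sided 0.05 (sidedness is not stated, so this is assumed):

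power = Φ{[d√n − 1.96√(2p̄(1−p̄))] / √(p₁(1−p₁) + p₂(1−p₂))}

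- 65% v 85%, n = 100: (2.000 − 1.200)/0.596 = 1.34, so power is 91.0% (92.3% at 105 per arm). The stated figure is 90%.
- 65% v 82%, n = 100: 78.2%; n = 105: 80.2%. The stated figure is 80%.

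Both reproduce within 2 points. Both refer to the unadjusted comparison.

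**2. Coefficients, intercept not counted.** Allocation 1 + nine single covariates 9 + clinical group 6 − 1 = 5 gives 15. This is a minimum, since comorbidity and severity may each need more than one term. The interaction adds 5, giving 20.

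**3. Untreated patients, 100 positives per arm.**

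| Control v POCT | Untreated | Per coefficient (15) | Per coefficient (20) |
|---|---|---|---|
| 65% v 85% | 35 + 15 = 50 | 3.3 | 2.5 |
| 65% v 91% | 35 + 9 = 44 | 2.9 | 2.2 |
| 50% v 85% (assumed) | 50 + 15 = 65 | 4.3 | 3.3 |

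The third row allows for the missed control diagnoses that the sample size section expects.

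**4. Bias by simulation.** The setting is 100 per arm, 65% v 85%, 1000 trials per row. Assumed: five continuous and four binary covariates; clinical groups equal, or 30/20/20/15/10/5%; covariate log odds ratios of size 0, 0.3 or 0.5. Means are over trials in which the model could be fitted. The true value is the covariate-conditional odds ratio.

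| Covariate effect, groups | True OR | ML mean (median) | Log-OR excess | Firth |
|---|---|---|---|---|
| 0, equal | 3.05 | 3.47 (3.39) | 11.4% | 3.07 |
| 0, unequal | 3.05 | 3.38 (3.26) | 9.2% | 3.01 |
| 0.3, equal | 3.43 | 4.02 (3.95) | 12.8% | 3.46 |
| 0.3, unequal | 3.42 | 3.96 (3.92) | 11.9% | 3.44 |
| 0.5, equal | 4.13 | 5.06 (4.78) | 14.2% | 4.16 |
| 0.5, unequal | 4.11 | 4.95 (4.76) | 13.2% | 4.07 |

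Means are exponentiated mean log odds ratios. Further results:

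- Coverage of the 95% interval over these rows is 92.5-94.8%. In one run at 105 per arm the excess is 11.1% and coverage 91.5%.
- At 65% v 91% (effect 0.3, unequal groups) the excess is 16.0%. At 50% v 85% it is 10.7%.
- With no treatment effect (2000 trials, 65% in both arms) the odds ratio is 0.99-1.01 and type I error 5.0-5.5%.
- A separate simulation (2000 trials, shares 18/22/22/15/15/8%) gives a median of 3.42 for the full model and 3.07 for a two-covariate model, against 3.05.

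**5. The interaction, if fitted to this outcome.** A group-by-arm cell with nobody untreated makes its term infinite. With group share s and treated proportion p, the chance of such a cell in one arm is (1 − s(1−p))^100. For equal groups:

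- POCT: (1 − 0.15/6)^100 = 0.0795
- Control: (1 − 0.35/6)^100 = 0.0025
- At least one of the 12 cells, treating cells as independent: 1 − (0.9205 × 0.9975)^6 = 40%

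The same formula gives about 73% for shares 30/20/20/15/10/5% and about 54% for 18/22/22/15/15/8%.

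The simulated failure rate of the interaction model is 41-53% (equal groups) and 77-84% (unequal). With shares 18/22/22/15/15/8%, a cell with everyone treated occurs in about 56% of trials. At 65% v 91% the failure rate is 96% with unequal groups. In the main-effects model at 65% v 85%, at least one coefficient fails in under 1% (equal) or 10-16% (unequal) of trials.

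**The case against.** The strongest reply is that this is a supportive analysis. The main comparison and the power statement are unadjusted, type I error holds, and interval coverage is only slightly low. The bias is also small beside sampling error: about 0.11 on the log scale (ln 3.42 − ln 3.05) against an unadjusted standard error of √(1/65 + 1/35 + 1/85 + 1/15) = 0.35. All of this stands, and it limits the weight of the point. It does not remove it, because the article commits to reporting this estimate.

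It is also fair that the interaction is optional and named for key secondary outcomes, some of which use the whole cohort. Twenty coefficients on 50 untreated patients arises only if the closing sentence is taken to cover the primary outcome. The only regression described above that sentence is the one for the primary outcome, so the reading is open but not certain.

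Four stronger readings are tempting and not supported:

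- **That omitting hospital and season inflates the odds ratio.** In a randomised comparison, leaving out a prognostic factor pulls a logistic odds ratio towards 1, and adding terms would worsen the sparsity. The article says "This service uses permuted blocks of varying sizes" and states no stratification factor, so the omission does not break with the design.
- **That patients with missing covariates will be lost.** The imputation rule applies "should missing data exceed 5% for the primary outcome or key secondary outcome measures". It says nothing of baseline covariates, but the article does not say such patients are dropped, and this is commonly settled in an analysis plan.
- **That antiviral use begun before randomisation is a missing covariate.** A patient who starts after admission but before randomisation has largely met the outcome already, so the term would itself cause separation.
- **That the whole gap between adjusted and unadjusted odds ratios is bias.** Part is legitimate: with covariate effects of 0.3, the conditional odds ratio is truly about 3.42 where the marginal one is 3.05.

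**Conclusion.** The point holds for the supportive adjusted model. At the planning rates it has about 3.3 untreated patients per coefficient, and ordinary maximum likelihood overstates its log odds ratio by about 9-14% when there is an effect. Firth's fit of the same 15 coefficients recovers the true value to within about 1.5% (3.01-3.07 against 3.05, for example), which identifies sparsity as the cause. If the interaction is fitted to this outcome, at least one term is not estimable in roughly 40-85% of trials at 65% v 85%.

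The counts follow from the article. The sizes of the bias and the failure rates rest on assumed covariate effects and clinical-group shares, since the article gives neither, and on reading multiple logistic regression as ordinary maximum likelihood. A reader might infer that the trial's primary conclusion is at risk. It is not: the unadjusted comparison, its power and its type I error are untouched.

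**What to change.** 1. Keep the unadjusted difference in proportions as the primary analysis, as now.
2. For the adjusted model, either fit the full list by Firth-penalised logistic regression, or prespecify a shorter covariate list with clinical group collapsed to fewer levels.
3. For the primary outcome, present subgroups as risk differences with confidence intervals by clinical group, or state that the interaction test is restricted to the key secondary outcomes.

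This is a change of wording, to be made before the data are analysed so that the choice does not depend on whether the model happened to fail. It needs no new data. The small downside is that, if the list is shortened, some covariates move to a sensitivity analysis.
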